#### Eligibility criteria for trial sites and surgeons

Only high-volume *trial sites* committing to include at least 10 patients per year will be chosen as trial sites.To ensure standardisation of the procedure and to minimise training effects, all *participating surgeons* must pass obligatory eLearning tutorials demonstrating the mesh-enforced loop ileostomy closure (experimental group) as well as non-mesh-based closure (control group) before participation in the trial.Furthermore, all *participating surgeons* must have performed a minimum of 10 loop ileostomy closures before participation in the trial. The number of previous ileostomy closures (<10 vs. ≥10) will be documented in the log staff for all participating surgeons.

### Who will take informed consent? {26a}

Patients scheduled for elective loop ileostomy closure are screened preoperatively. An authorised physician with a GCP training will inform the patient about the trial (visit 1). Patients are enrolled given their ability to understand the extent and nature of the trial as well as their written informed consent after detailed patient information.

### Additional consent provisions for collection and use of participant data and biological specimens {26b}

No biological samples will be collected during the trial.

## Interventions

### Explanation for the choice of comparators {6b}

Patients in both groups will receive ileostomy closure according to the current standard of care, i.e. direct fascia closure according to the small-stitch technique with a slowly absorbable suture. In addition, in the intervention group, the abdominal wall closure will be augmented with a non-absorbable, macro-pore light-weight mesh. Patients in the intervention group might therefore benefit from a potential decreased IH rate; however, the efficacy of the experimental intervention has not yet been shown. A real clinical equipoise exists between the two comparators (see the “Introduction” section).

### Intervention description {11a}

#### Experimental intervention

The re-establishment of intestinal continuity will be achieved by either stapled or by hand-sewn anastomosis, according to the surgeon’s preference, and the bowel will be positioned back into the peritoneal cavity.Changing of surgical gloves must be performed before mesh implantation. Either after surgical stoma closure or, latest, before mesh placement.A retromuscular space is created by blunt dissection overlapping the suture line in cranio-caudal direction by 4–6cm. In the medial-to-lateral direction, the dissection is limited by the linea alba and linea semilunaris in case the stoma is placed within the rectus sheath. In case the stoma is outside the rectus sheath or below the linea arcuata (no posterior rectus sheath), a retromuscular space should be formed by dissection overlapping the future fascial suture line by 4–6cm in all directions.The posterior rectus sheath (if the stoma is within the rectus sheath) will be closed with a continuous polydioxanone suture (PDS Plus, USP 2-0) with tissue bites of 5 mm and intersuture spacing of 5 mm applied exclusively to the fascia omitting subcutaneous fat and muscle tissue (small-stitch technique, SST). In case the stoma is outside the rectus sheath or below the linea arcuata (no posterior rectus sheath), the posterior abdominal wall should be closed with a continuous polydioxanone suture (PDS Plus, USP 2-0) with tissue bites of 5 mm and intersuture spacing of 5 mm applied exclusively to the fascia omitting subcutaneous fat and muscle tissue (small-stitch technique, SST).The retromuscular space should be irrigated with 500 ml of sterile fluid (lavage) before mesh placement. The type of solution is at the discretion of the surgeon, e.g. saline solution (NaCl 0.9%), Ringer’s or any antiseptic solutions like polyhexanide (PHX), Lavanox or others can be used for this purpose as long as its application is approved for this purpose.A non-absorbable, macro-pore (pore size ≥ 1000μm [23] or effective porosity >0% [24]) light-weight monofilament (class Ia) or mixed structure (class Ic) mesh [24] is placed in the retromuscular position. The size of the mesh should overlap the suture line of the posterior rectus sheath by 4–6cm on all sides. In the medial-to-lateral direction, the mesh size might be limited by the linea alba and linea semilunaris (medial and lateral walls of the rectus sheath). To avoid any commercial interest of a single company, no specific mesh, but rather a well-described uniform CE-certified mesh class must be used in this trial. The safety of this class of meshes has already been shown in prospective trials in abdominal wall repair and ostomy formation [15].The mesh should be fixed to the posterior fascia tension-free with single knots if deemed necessary by the operating surgeon. The suture material is at the discretion of the operating surgeon.The rectus muscle should *not* be closed/approximated by sutures.The anterior rectus sheath will be closed in the same manner as the posterior sheath with a continuous polydioxanone suture (PDS Plus, USP 2-0) with tissue bites of 5 mm and intersuture spacing of 5 mm applied exclusively to the fascia omitting subcutaneous fat and muscle tissue (small-stitch technique, SST).Subcutaneous drains can be placed at the discretion of the operating surgeon.The skin will be closed according to the surgeon’s preference (suture, staples, pursestring).Further perioperative and postoperative treatment will be equal for both groups according to the respective local standard of care.

#### Control intervention

The re-establishment of intestinal continuity will be achieved either by staples or by hand-sewn anastomosis, according to the surgeon’s preference, and the bowel will be positioned back into the peritoneal cavity.Changing of surgical gloves.The posterior rectus sheath (if the stoma is within the rectus sheath) will be closed with a continuous polydioxanone suture (PDS Plus, USP 2-0) with tissue bites of 5 mm and intersuture spacing of 5 mm applied exclusively to the fascia omitting subcutaneous fat and muscle tissue (small-stitch technique, SST). In case the stoma is outside, the rectus sheath or below the linea arcuata (no posterior rectus sheath), the posterior abdominal wall should be closed with a continuous polydioxanone suture (PDS Plus, USP 2-0) with tissue bites of 5 mm and intersuture spacing of 5 mm applied exclusively to the fascia omitting subcutaneous fat and muscle tissue (small-stitch technique, SST).The rectus muscle should *not* be closed/approximated by sutures.The *anterior* rectus sheath will be closed with a continuous polydioxanone suture (PDS Plus, USP 2-0) with tissue bites of 5 mm and intersuture spacing of 5 mm applied exclusively to the fascia omitting subcutaneous fat and muscle tissue (small-stitch technique, SST).Subcutaneous drains can be placed at the discretion of the operating surgeon.The skin will be closed according to the surgeon’s preference (suture, staples, pursestring).Further perioperative and postoperative treatment will be equal for both groups according to the respective local standard of care.

### Criteria for discontinuing or modifying allocated interventions {11b}

As P.E.L.I.ON. is investigating two surgical interventions, no criteria for discontinuing or modifying the allocated intervention are applicable.

### Strategies to improve adherence to interventions {11c}

As P.E.L.I.ON. is investigating two surgical interventions, strategies to improve adherence to the intervention are unnecessary as the patient cannot “withdraw” from the intervention during surgery.

### Relevant concomitant care permitted or prohibited during the trial {11d}

Further perioperative and postoperative treatment will be according to the local standard of care. This also includes the use of abdominal belts which is at the discretion of the operating surgeon. There will be no restrictions for additional treatments during the trial.

### Provisions for post-trial care {30}

For trials that are conducted according to the Medical Association’s professional code (Berufsordnung der Bundesärztekammer) § 15, there is no obligation for a specific trial liability insurance. However, patients will be insured against travel accidents for their follow-up visits (*Wegeversicherung*). No other specific post-trial care and no specific compensation to those who suffer harm from trial participation are implemented. Post-trial care will follow the clinical standard of care at the respective sites.

### Outcomes {12}

#### Primary outcome measure

An *incisional hernia* at the ileostomy closure site within 2 years of follow-up represents an outcome with the highest long-term impact for the patient and the healthcare system and is therefore selected as the primary endpoint. The duration of follow-up (2 years) is recommended by the EHS as the rate of IH increases after 1 year [25]. Furthermore, the primary endpoint is recommended by the EHS as it is clearly measurable and reproducible. Consequently, “any abdominal wall gap with or without a bulge in the area of a postoperative scar perceptible or palpable by clinical examination or imaging” is regarded as an IH*.*

Patients will be assessed for the primary endpoint at 12 and 24 months after the trial intervention. At these dates, patients will be examined by a clinician blinded for the trial intervention and by a radiologic examination performed by a blinded assessor. Radiologic exams allowed for assessment in the trial are for example sonography, computed tomography (CT) or magnetic resonance imaging (MRI) scans. To reduce radiation exposure, sonography is the preferred imaging method. No radiation-associated imaging should be initiated solely for the purpose of the P.E.L.I.O.N trial. However, results of radiation-associated imaging like CT scans that are performed for other indications (e.g. oncological follow-up) can be used in the trial. In this case, an additional ultrasound of the abdominal wall is not necessary. In case of conflicting results between clinical and radiologic exams, the radiologic imaging is decisive to increase sensitivity [25]. If only one of the two examinations is performed (i.e. either clinical or imaging), the result of this assessment will be used for analysis. As many patients included in this trial are expected to have an oncological indication and the included centres perform their oncological follow-up themselves, the loss to follow-up of patients is expected to be low. Possible results of the primary outcome assessment are listed in Table 2.

**Table 2 Tab2:** Possible outcomes of clinical and radiological hernia assessment and outcome decisions in the P.E.L.I.O.N. trial

Clinical exam result	Imaging result	Primary endpoint
**Hernia**	Hernia	**Hernia**
**No hernia**	Hernia	**Hernia**
**Hernia**	No hernia	No hernia
**No hernia**	No hernia	No hernia
**Hernia**	Missing	**Hernia**
**No hernia**	Missing	No hernia
**Missing**	Hernia	**Hernia**
**Missing**	No hernia	No hernia

For patients who are unable or unwilling to attend the follow-up visits, a telephone follow-up is incorporated. As the patient-reported outcome questionnaire developed by Tastaldi et al. (Hernia Recurrence Inventory, HRI) was modified and will be used in all patients [26], it can be used as a screening tool during telephone visits, i.e. patients who are suspected to have an IH based on the questionnaire might be convinced to attend an outpatient visit, even if they were reluctant to do so before. Time-to-event analyses for the primary endpoint are not justified as it is highly dependent on the density of the follow-up schedule and clinical symptoms and our interest is whether a hernia occurs rather than when a hernia occurs.

#### Secondary outcome measures

Postoperative complications within 30 days according to the Dindo-Clavien classification (DCC) ≥3 [27]Number of surgical site occurrences (SSO) [28] defined as the sum of the following *individual* secondary endpoints:*Superficial or deep surgical site infections* (SSIs) within 1 year after index operation according to the CDC definition [29]. Follow-up for this endpoint will be 1 year as defined by the CDC in case of foreign body placement [29]. Organ-space SSIs are excluded in this measurement as they are independent of the abdominal wall closure technique, but rather depend on the underlying surgery. Furthermore, they are infrequent after ileostomy reversal. In addition, clinically relevant organ-space SSIs (defined as Dindo-Clavien ≥ grade 3) will be recorded in the overall complication rate according within 30 daysRate of *wound seromas* at former ostomy site within 30 days after index operation. Seroma will be defined as a collection of serous fluid in a dead space, which can either be in situ or leaking through a wound [30]. Assessment can be by clinical or radiologic examinationRate of *wound hematomas* at former ostomy site within 30 days after index operation. Hematomas are defined as an accumulation of blood in the wound area, which warrants (bedside) surgical exploration and intervention [31]*Enterocutaneous fistulas* within 24 months after index operation [28]Number of patients undergoing *incisional hernia repair* at the site of ileostomy closure within 24 months after the index operationNumber of *revision surgeries* because of complications related to ileostomy closure within 24 months after the index operation*Chronic postoperative pain* in the ileostomy closure site during follow-up measured via the Pain Questions of the modified EHS-QoL questionnaire at 12 and 24 months [32]*Health-related quality of life* at baseline, 12 and 24 months after index operation according to the EHS-QoL questionnaire [32]*Modified Hernia Recurrence Inventory (HRI)* at 12 and 24 months [26]

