For ostomy reversal, much less evidence is available. Probably because concerns of safety have been voiced regarding an increased risk of surgical site infections (SSI) and mesh infections. Three non-randomised studies have been published on prophylactic mesh placement for ostomy reversal [16–18]. Overall, these three studies showed an overwhelming reduction of IH in the prophylactic mesh group compared to no mesh placement in a systematic review (OR 0.10, 95% CI 0.04–0.27, *p* < 0.001, I2 = 0%, CI 0–91.40%) [19]. However, two of the three studies were retrospective analyses, none of the studies was randomised, follow-up and endpoint assessment were inadequate and studies were at high risk of bias [19]. Furthermore, the technique varied widely between the studies. However, none of the studies showed an increase in the rate of SSI for patients undergoing prophylactic mesh placement at the site of stoma reversal, thus indicating the safety of the technique.

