### Adverse event reporting and harms {22}

Since trial interventions in P.E.L.I.O.N are medical routine, and the trial is conducted under the Medical Association’s professional code (Berufsordnung der Bundesärztekammer) §15, there is no need to record every adverse event. Instead of documenting serious adverse events (SAE), the following secondary endpoints will be used to assess safety in the P.E.L.I.O.N trial:Postoperative complications within 30 days according to the Dindo-Clavien classification (DCC) ≥3 [27]Superficial or deep surgical site infections (SSIs) within 1 year after index operation according to the CDC definition [29]Rate of wound seromas at former ostomy site within 30 days after the index operationRate of hematomas at former ostomy site within 30 days after the index operationEnterocutaneous fistulas within 24 months after the index operation [28]Number of revision surgeries because of complications related to ileostomy closure within 24 months after the index operation

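### After month 12 an infection at the closure site is counted only if it leads to revision surgery or an enterocutaneous fistula, and mesh infection has no endpoint of its own.

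*Protocol article*

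**What the plan says.** The background section of the Protocol article explains the thin evidence on mesh at ostomy reversal by noting that "concerns of safety have been voiced regarding an increased risk of surgical site infections (SSI) and mesh infections". The section on the choice of comparators says that in the experimental arm "the abdominal wall closure will be augmented with a non-absorbable, macro-pore light-weight mesh".

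Under Secondary outcome measures, the SSI endpoint covers superficial and deep infections. On its duration: "Follow-up for this endpoint will be 1 year as defined by the CDC in case of foreign body placement". On the third depth category: "Organ-space SSIs are excluded in this measurement as they are independent of the abdominal wall closure technique". Part of that category is picked up elsewhere, since "clinically relevant organ-space SSIs (defined as Dindo-Clavien ≥ grade 3) will be recorded in the overall complication rate", within 30 days.

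Table 3 (Trial visits) schedules SSI assessment at visits 3–5 and at month 12, and marks it as not done at month 24. Hernia assessment, fistula, hernia repair and revision surgery are all scheduled at both month 12 and month 24.

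The section on adverse events and harms states that "there is no need to record every adverse event" and uses six secondary endpoints in place of serious adverse event documentation. One is "Number of revision surgeries because of complications related to ileostomy closure within 24 months after the index operation". Enterocutaneous fistula is also followed to 24 months. Neither mesh infection nor mesh removal is on the list.

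**The concern.** Efficacy is measured to 24 months, but infection, the harm that the protocol itself links to the mesh, is measured to 12. In a trial with general adverse event reporting, a late infection treated without an operation would at least appear as an adverse event. Here that route is closed, so such an infection need not be recorded at all.

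The loss is unlikely to be even between the arms. Only the experimental arm is assigned a permanent implant, so late infections connected with it would go unrecorded mainly there. The infection comparison would then lean towards showing no excess with mesh. That comparison matters because the abstract says that mesh could become the new standard. The data safety and monitoring board has the same gap: it reviews surgical site occurrences, whose SSI component ends at one year, and major complications within 30 days.

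**Working it through.** This is a question of coverage, so the check takes each kind of infection and asks which listed endpoint would count it. The inputs are Secondary outcome measures, Table 3 and the harms section.

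- **Superficial or deep, up to month 12:** counted as SSI, whether operated on or not.
- **Superficial or deep, months 12 to 24:** the SSI endpoint has ended. Counted only through revision surgery or enterocutaneous fistula.
- **Organ-space, up to day 30, Dindo-Clavien grade 3 or higher:** counted in the overall complication rate. The text does not require revision surgery.
- **Organ-space, up to day 30, below grade 3:** not counted as an infection, by stated exclusion.
- **Organ-space, after day 30:** counted only through revision surgery or fistula.
- **Any other route:** none, because general adverse event and serious adverse event recording is replaced by the list.

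The second row is the gap. It covers 24 − 12 = 12 months, half of the follow-up.

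**Where a mesh infection would fall.** In the experimental procedure, "A retromuscular space is created by blunt dissection overlapping the suture line in cranio-caudal direction by 4–6cm", the posterior layer is closed, and the mesh is placed in front of it, behind the muscle. The mesh therefore lies inside the abdominal wall. The reason given for the organ-space exclusion is that such infections do not depend on how the wall is closed. Read together, these suggest that mesh-layer infection belongs under superficial or deep SSI, but the protocol does not say so.

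**Which arm loses more.** The assigned procedures differ in the implant. Dissection of the retromuscular space is described only for the experimental arm, but randomisation takes place after closure of the posterior layer, so some controls may also have been dissected. The argument for an uneven loss therefore rests on the mesh itself.

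**Scale.** The plan gives no figure for mesh infection to reproduce. The group size is consistent: 121 per group with 20% loss gives 121 / 0.80 = 151.25, rounded up to 152. Cases missed = assumed rate × patients. The rates are assumptions that show scale only:

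- 152 patients: 0.005 × 152 = 0.76, and 0.03 × 152 = 4.56.
- 121 patients, if the planned 20% are lost: 0.005 × 121 = 0.6, and 0.03 × 121 = 3.6.

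**The case against.** The strongest reply is that the one-year window is a reasoned choice. It follows the CDC rule for foreign bodies, applies to both arms and agrees with Table 3. That stands: the protocol does not contradict itself, and the one-year count should be kept. It does not explain why nothing on infection is recorded at a visit where fistula and revision surgery are.

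Three stronger readings are tempting, and the documents do not support them.

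- **That late or organ-space infections are counted nowhere.** Organ-space infections of grade 3 or higher within 30 days are counted, fistulas are counted to 24 months whether operated on or not, and surgical mesh removal for infection would fall under revision surgery.
- **That mesh infections would be lost by being graded organ-space.** This needs an assessor to put an infection inside the abdominal wall into that category. The protocol nowhere says this would happen, and the cited CDC definition is not at hand. Only the missing statement of where mesh-layer infection belongs can be shown.
- **That every patient is examined and imaged at month 24.** Telephone follow-up is allowed for those who do not attend, and one examination, clinical or imaging, is enough for the hernia endpoint.

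It is also fair to say that secondary outcomes are analysed descriptively, so no confirmatory conclusion on infection is at stake, and that the full protocol may hold case report form detail such as the reason for a revision. Such detail would not restore an SSI assessment that Table 3 leaves out.

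**Conclusion.** The point holds in a limited form. Mesh infection is a named risk without an endpoint, and a superficial or deep infection at the closure site in months 12 to 24 reaches a listed endpoint only through revision surgery or an enterocutaneous fistula. The direction of the under-count, mainly in the mesh arm, rests on the assumption that late infection is more frequent around a permanent implant. Its size cannot be derived from the documents. The assumed range of about 1 to 5 missed cases among 152 is not evidence of material bias.

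The primary endpoint and its analysis are unaffected. This is a cheap improvement to safety measurement and does not amount to a flaw in the design. It is best made during follow-up, since an infection that was treated and has healed may be hard to recover afterwards.

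**What to change.** 1. In Table 3, also assess superficial and deep SSI at month 24, asking about the whole interval since month 12. A blinded assessor does this at the visit, or by telephone where the patient does not attend, with the mode of contact recorded.
2. Report SSI to 24 months as an additional safety line. Leave the one-year CDC endpoint and the surgical site occurrence sum unchanged.
3. Under Secondary outcome measures, add one sentence stating that infection in the retromuscular or mesh layer of the abdominal wall counts under the SSI endpoint. Intra-abdominal organ-space infection stays excluded as now, so that infections arising from the bowel anastomosis do not dilute the comparison.
4. Have unblinded staff record mesh involvement and partial or complete mesh removal to 24 months. These items reveal the arm, so the blinding section, which requires blinded assessors for all outcome assessments, needs a sentence that places them outside the blinded assessment.

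The cost is one more item at an existing visit, a short entry by unblinded staff, and a second SSI count that must be labelled clearly. Telephone answers will be less reliable than an examination.
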